## Role of sponsor {5c}

This is an investigator-initiated study. The sponsor as initiating study site has implemented the study design, data collection, management, analysis and interpretation of data. Preparation of the manuscript and the decision to submit was made by the sponsor.

## Recruitment {15}

Many patients with back pain and specifically sacroiliac joint pain are assigned to specialized outpatient clinics with focus on neuromodulation once a week. The study team is always part of the neuromodulation outpatient clinics, so that patients meeting eligibility criteria are immediately in contact with the investigators. The research coordinator will provide information material describing the study as well as sacroiliac PNS models.

After detailed verbal information, the participants are given a sufficient cooling off period and the opportunity for open questions afterwards. Undecided patients are able to contact a study nurse, making participation on a later time possible. Patients who provide written informed consent to participate in the study will be randomized as described before.

## Patient and public involvement

Although this study might be from relevant public interest due to the high prevalence of SIJP and impact on total working force loss in Germany, there was no patient or public involvement in the design of the study protocol.

## Assignment of interventions: allocation

### Sequence generation {16a}

Participants will be randomized in a 4:3 ratio to either to the PNS group or BMT group (current gold standard).

Randomization is performed by the study team using computer-generated randomization lists with variable block sizes. No stratification is used.

### Concealment mechanism {16b}

Allocation sequence is performed electronically using RedCap prior to the randomization of the participants. After randomization, further concealment is not possible due to the nature of the study.

### Implementation {16c}

Enrollment of participants is done by the investigator or study coordinator. Assignment to intervention is determined by the randomization group. The allocation sequence is performed electronically as described previously. Allocation is therefore not predictable for the study team before randomization.

## Assignment of interventions: blinding

### Who will be blinded {17a}

As patients will be aware of the allocated study arm after randomization, blinding is not possible.

### Procedure for unblinding if needed {17b}

Does not apply.

## Data collection and management

### Plans for assessment and collection of outcomes {18a}

Regular visits for participants are planned on day 0, after 3 months (± 30 days), 6 months (± 30 days) and 12 months (± 60 days). Additionally, patients allocated to the PNS group are evaluated after the trial phase.

The primary and secondary outcome measurements will be acquired by the study group on the visits as described in the study schedule in Table 1. Additionally, ODI (Oswestry Disability Index), NRS (Numeric Pain Rating Scale), SF-36 (The Short Form (36) Health Survey), PSQI (Pittsburgh Sleep Quality Index), ADS-K CES-D (Center of Epidemiological Studies Depression Scale), IPG data and neurological status will be assessed at all scheduled visits.

### Plans to promote participant retention and complete follow-up {18b}

The study group will contact participants by mail and phone throughout the trial and arrange all appointments with participation in this study. The reported scope of 30–60 days in the 3-, 6- and 12-month outpatient visits gives more flexibility to the participants. The importance of the visits is explained to participants in advance. Participants have the opportunity to contact the study nurse at any time for questions concerning follow-up. If participants want to withdraw from the study, a final outpatient visit is scheduled in order to complete data collection.

### Data management {19}

All data are stored in an encrypted form in the REDCap (Research Electronic Data Capture) database. IPG data are recorded by the technical assistants and transferred to the same database. Password protection ensures that only authorized persons from the study have access to participants data. Data collection will be done in the outpatient visits, so that there will be no need for questionnaires by post or mail.

### Confidentiality {27}

All collected personal and medical data will be coded and recorded by the rules of good clinical practice. Disclosure to others than the study team is prohibited. Participants will receive a unique study ID so that data will be stored anonymously. As described previously, the database is secured with a password. Only the steering committee and the study team members when this is necessary in the interest of the trial will have access to the anonymized data.

### Plans for collection, laboratory evaluation and storage of biological specimens for genetic or molecular analysis in this trial/future use {33}

Storage of biological specimens is not conducted in this trial.

## Statistical methods

### Statistical methods for primary and secondary outcomes {20a}

The primary endpoint will be analysed by mixed linear regression with the change in NRS score from baseline to 6 [12] months as dependent and treatment and baseline value as independent variables. Study center will be added as a random intercept. In order to adjust for relevant covariables, a maximum of four additional variables are included in the model due to the sample size limitations. By this procedure, depending on the correlation of the independent variables with the dependent variable, a gain in power is obtained compared with the calculated sample size [14]. Even in the worst case and a correlation of 0, however, at least the power as specified in the sample size calculation is achieved. As a further analysis to investigate time trends, we will apply a linear mixed effects models as before but consider all time points and include timepoint as an additional, discrete factor. Further, the interaction between treatment and timepoint and a random intercept for the patients will be added.

A chi-square test is used to analyse the proportion of patients with at least a 50% reduction in the NRS value. In a second step, if there are enough patients with a corresponding reduction, a mixed logistic regression model with additional covariates and study center as random intercept is created. The secondary endpoints will be analysed analogously to the primary endpoint. All analyses including *p*-values are to be considered purely exploratory. All results will be reported with 95% CIs.

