## Sample size {14}

Based on our own preliminary data of 10 patients, a mean decrease in NRS score of 3.5 points (standard deviation = 3.1) was observed in the PNS group, whereas the reduction in the BMT group was 1.4 points (standard deviation = 1.7). Childs et al. have previously reported a 2-point difference on the NRS to be clinically meaningful in a multicenter, randomized trial [13].

To detect the observed difference (2.1 points in reduction in NRS score) with an estimated standard deviation of 3, a two-sided error of 5% with a power of 80% using an unpaired *t*-test, a case number of 34 per group is needed. Thus, taking into account the 25% non-responders in the PNS group, one would need 46 patients in the intervention group and use a randomization of 4:3 accordingly. Adding 10% additional dropouts, one would need to include a total of 90 patients (52 in the PNS group and 38 in the BMT group) in the study. The sample size planning was performed using nQuery version 7.0. The planning in this study was performed by the study sponsor in collaboration with the local Institute of Biometry and Clinical Epidemiology.

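### The adjusted model does not keep at least the specified power at zero correlation: with the maximum of five unrelated covariates, 34 per group gives about 78%, not 80%

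*Protocol article*

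**What the plan says.** The Sample size section {14} of the protocol article plans for an unpaired t-test, a difference of 2.1 NRS points, "with an estimated standard deviation of 3", a two-sided 5% level and 80% power, and concludes that "a case number of 34 per group is needed".

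The section on statistical methods for primary and secondary outcomes {20a} uses a different analysis: a mixed linear regression of the change in NRS on treatment and baseline value, with a random intercept for centre. To this, "a maximum of four additional variables are included in the model due to the sample size limitations". The model therefore has at most five covariates besides treatment. The section expects adjustment to raise power, depending on how strongly the covariates correlate with the outcome, and adds a floor: "Even in the worst case and a correlation of 0, however, at least the power as specified in the sample size calculation is achieved".

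Sequence generation {16a} states that randomisation is not stratified.

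**The concern.** The sentence gives adjustment no downside: it can raise power and can never take it below the planned figure. That is the large-sample picture, in which residual variance is multiplied by one minus the squared correlation and zero correlation returns the t-test. In a trial of 68 evaluable patients, a covariate unrelated to outcome has a cost. It uses a degree of freedom, and its chance imbalance between arms inflates the variance of the treatment estimate. The calculation has little slack to absorb this, because 33 per group already falls just short of 80%.

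At stake is a stated power property that the design lacks in the very case the sentence names. The sentence also tells whoever selects the four additional covariates that weak ones are free.

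**Working it through.** **Inputs**, all from the protocol article: difference 2.1, SD 3, two-sided 5%, target power 80% and 34 evaluable per group (Sample size {14}); baseline NRS plus at most four covariates, so k from 1 to 5, with covariate–outcome correlation 0 ({20a}); no stratification, so covariates are balanced by chance only ({16a}).

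**Step 1: reproduce the plan's figure.** For the two-sample t-test the noncentrality is 2.1 / (3 × √(2/34)) = 2.886 on 66 degrees of freedom. From the noncentral t distribution:

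- 33 per group: 79.97%
- 34 per group: 81.2%

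The smallest group size that reaches 80% is 34, as the plan states.

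**Step 2: add k covariates unrelated to outcome.** With N = 68:

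- Residual degrees of freedom are N − 2 − k.
- The variance of the treatment estimate is multiplied by 1/(1 − R²). Here R² is the chance association of treatment with the covariates, distributed as Beta(k/2, (N − 1 − k)/2).
- The mean of that multiplier is (N − 3)/(N − 3 − k). For k = 5 this is 65/60 = 1.083, an average variance inflation of about 8%.
- Residual variance does not fall, because the correlations are zero.

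Power averaged over the distribution of R²:

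| Unrelated covariates (k) | Power at 34 per group |
|---|---|
| 0 (t-test) | 81.2% |
| 1 (baseline NRS only) | 80.6% |
| 2 | 79.9% |
| 3 | 79.3% |
| 4 | 78.6% |
| 5 (stated maximum) | 77.9% |

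A simulation of 60,000 trials per scenario gives 81.0% (k = 0), 80.4% (k = 1) and 77.9% (k = 5).

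**Step 3: source of the loss.** Removing five degrees of freedom with no imbalance leaves 81.1%. Nearly all of the 3.2-point drop (81.2 − 77.9, before rounding) is therefore chance imbalance.

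**Step 4: break-even for k = 5.** If the covariates jointly explain a share of outcome variance, the SD is multiplied by √(1 − share):

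- 5% explained: 79.97%
- 6% explained: 80.4%

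Power of 80% is restored at slightly more than 5%, equivalent to one covariate with a correlation of about 0.23 (0.23² = 0.053). Alternatively, 36 per group with five unrelated covariates would give 80.5%.

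**Not modelled:** the random centre intercept, because the article gives neither the number of centres nor a between-centre variance.

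**The case against.** **Corner case.** The shortfall needs all four optional covariates, and all five covariates (baseline NRS included) unrelated to the change in NRS. With baseline alone, the only covariate fixed by the plan, the sentence is true. A modest joint correlation restores 80%. All of this stands and keeps the point small. It does not rescue the sentence, which names zero correlation as its worst case and sets no condition on the number of covariates.

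**Limited consequence.** Section {20a} calls all analyses exploratory. The planning SD of 3 also looks cautious beside the pilot SDs of 3.1 and 1.7, whose equal-weight pooled value is √((3.1² + 1.7²)/2) = 2.5; at that SD, five unrelated covariates would still leave 90.5%. This too limits the weight. But the guarantee refers to the specified power, which was calculated at SD 3.

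**More patients than 34 per group.** The plan inflates the intervention arm: "taking into account the 25% non-responders in the PNS group, one would need 46 patients in the intervention group". With 46 against 34 analysed and the full 2.1-point difference, five unrelated covariates give 84.0%, so on that reading the floor holds. A reader might infer the opposite, that the non-responders dilute the effect and true power is far below 80%. If 25% of the PNS arm gained nothing over BMT, the difference would be 0.75 × 2.1 = 1.575 and power about 60% with five unrelated covariates (63% with none). The documents support neither reading as the basis for this point. They do not say whether the pilot mean already includes non-responders, nor what outcome explanted patients are expected to have. Most of that drop would come from assumed dilution and only about 3 points from covariates. It is a separate sample-size question. The specified power rests on 34 per group, and that is the fair test of the sentence.

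**Conclusion.** The guarantee is wrong as written. At 34 evaluable per group, difference 2.1, SD 3 and two-sided 5%, it holds for baseline NRS alone, fails marginally at two unrelated covariates and misses the specified 80% by 2.1 points at the maximum of five.

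This assumes covariates balanced only by chance and exactly zero correlation, the case the sentence itself describes; the centre effect is left out. The finding does not show that the trial is underpowered or that adjustment is a poor choice. A reader might infer either, but adjustment gains power once the covariates carry modest prognostic information. The documents give no correlation between baseline NRS and its change, so whether they will do so here cannot be stated. The error is in the unqualified wording.

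**What to change.** In section {20a}, delete the sentence claiming at least the specified power at zero correlation. In its place, state that:

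- with five covariates unrelated to outcome, power at 34 evaluable patients per group is about 78%;
- the covariates must jointly explain slightly more than 5% of outcome variance to restore 80%;
- the additional covariates, four at most, are chosen for expected prognostic value.

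The replacement should not assert that baseline NRS will pass the 5% mark unless the sponsor has data to show it.

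The cost is one or two sentences and a slightly less favourable stated figure. Enrolment and the planned analysis are unchanged.

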## Objectives {7}

The primary objective of this study is to evaluate the influence of peripheral nerve stimulation on the pain level, pain-associated disability and quality of life in patients with chronic intractable SIJP with a high evidence level. It is hypothesized that PNS of the rami dorsales (L5–S3) in patients with chronic sacroiliac joint pain is superior compared to the best medical treatment 6 months after therapy.

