### Outcomes {12}

The primary outcome is the difference in Numeric Pain Rating Scale (NRS) between baseline and after 6 months.

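### The analysis section makes every p-value exploratory, with no exception for the primary endpoint, which contradicts the 6-month superiority hypothesis and the two-sided 5% sizing

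*Protocol article*

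**What the plan says.** Four places in the protocol article set up a confirmatory comparison.

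- **Objectives {7}** states the hypothesis that PNS "is superior compared to the best medical treatment 6 months after therapy" and aims for evidence of a high level.
- **Outcomes {12}** names one primary endpoint: "The primary outcome is the difference in Numeric Pain Rating Scale (NRS) between baseline and after 6 months". The 12-month NRS, the responder proportion, disability and quality of life are listed as secondary.
- **Sample size {14}** plans for "a two-sided error of 5% with a power of 80" percent, using an unpaired t-test.
- **Statistical methods for primary and secondary outcomes {20a}** specifies a mixed linear regression for the primary endpoint. It argues that this model has at least the power of the sample size calculation.

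The same {20a} section then closes with a rule that applies to everything in it: "All analyses including *p*-values are to be considered purely exploratory". It adds that results will carry 95% confidence intervals.

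**The concern.** A sample size set by a type I error rate and a power describes a test with a decision rule: superiority is concluded if the test rejects. The exploratory sentence removes that rule for every analysis, and it stands in a section whose heading covers the primary outcome. The protocol therefore gives two incompatible answers to whether the trial is meant to confirm its hypothesis.

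What is at stake is the status of the main result. If the investigators follow {20a}, a significant 6-month difference cannot be presented as confirmed superiority, although that is the hypothesis in the Objectives and although the Abstract and Discussion promise high evidence. If they claim superiority anyway, they depart from their own plan, and a reader cannot tell whether the choice was made before or after the data were seen.

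**Working it through.** **Step 1. Is the sizing a real test plan?** The inputs come from Sample size {14}: "To detect the observed difference (2.1 points in reduction in NRS score) with an estimated standard deviation of 3", two-sided alpha 0.05, power 0.80, unpaired t-test.

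- Standardised effect: 2.1 / 3 = 0.70.
- Normal approximation: n = 2 × (1.960 + 0.842)² / 0.70² = 2 × 7.85 / 0.49 = 32.04, rounded up to 33 per group.
- Noncentral t-test: 33.02, rounded up to 34 per group. Power is 80.0% at 33 (0.7997, just short of the target) and 81.2% at 34.
- The plan says "a case number of 34 per group is needed", so its figure is reproduced.
- Allowance for 25% non-responders in the PNS group: 34 / 0.75 = 45.3, rounded up to 46. This matches the plan, and 34 × 4/3 = 45.3 explains the 4:3 ratio.
- Dropout of 10%: 46 / 0.9 = 51.1, rounded up to 52; 34 / 0.9 = 37.8, rounded up to 38. The total is 52 + 38 = 90, as stated.

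The enrolment target therefore follows directly from a two-sided 5% test with 80% power. It was not set by feasibility or by the precision of an estimate.

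**Step 2. Set the statements side by side.**

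| Section | Status it gives the 6-month NRS comparison |
|---|---|
| Objectives {7} | Subject of a superiority hypothesis |
| Outcomes {12} | The only primary endpoint |
| Sample size {14} | Tested at two-sided 5% with 80% power |
| Statistical methods {20a}, power remark | Tested with at least the planned power |
| Statistical methods {20a}, closing rule | Exploratory, like all other analyses |

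The first four rows agree with each other. The fifth contradicts them, and no other section says that one test is confirmatory or gives a decision rule for superiority.

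**Step 3. Does either resolution change a number?** No. If the 6-month comparison is named as the one confirmatory test at two-sided 5%, it is the test for which the trial is already sized, so N stays at 90. If the superiority claim is withdrawn, the sample size again need not change.

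**The case against.** **The sentence may concern only the secondary endpoints.** It directly follows the statement that these are analysed like the primary one, and earlier in the section the authors defend the power of the primary model, which fits a planned primary test. This may well be the intent, and it is the best argument for treating the matter as loose drafting. But the words cover all analyses, under a heading that names the primary outcome. If something narrower was meant, the text is wrong as it stands and needs the same correction.

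**A statistical analysis plan may settle it.** That would be a good answer to an omission. Here the protocol states a rule, and an analysis plan that named a confirmatory test would contradict it.

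**A cautious label is not a statistical error.** This is true in itself. A trial may be sized formally and still report its p-values descriptively with confidence intervals. The label limits the strength of the claim; it does not prevent a prespecified randomised difference from being reported as evidence. What does not fit is the label together with a superiority hypothesis and a promise of high evidence.

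**Stronger readings that the documents do not support.**

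- A reader might infer that, with no confirmatory test, all outcomes carry equal standing. They do not: the protocol keeps a clear hierarchy of one primary outcome and listed secondary ones, and only NRS reduction drives the sample size.
- A reader might count eight comparisons (NRS, responder, disability and quality of life, each at 6 and 12 months) and compute 1 − 0.95⁸ = 0.337 as the chance of a false positive. That is the value under independence, not an upper bound (the Bonferroni bound is 8 × 0.05 = 0.40). Independence is implausible, because responder status is derived from the same NRS scores and both time points come from the same patients. Above all, the figure measures the risk of a confirmatory claim resting on any of the eight, which the exploratory label itself disclaims.
- A reader might take the bracketed 12 after the 6 in the primary-model sentence as a second primary time point. The Abstract, Objectives and Outcomes all fix 6 months. The bracket may be shorthand for the secondary 12-month analysis or a stray citation mark, since the article uses square brackets for citations. It needs clarifying, no more.

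**Conclusion.** The contradiction is real and should be resolved before analysis. As written, {20a} withdraws from the primary comparison the confirmatory status that {7}, {12} and {14} give it, so a significant 6-month result could not be claimed as confirmed superiority under the protocol's own rule.

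Its size is not a number: no power, error rate or sample size in the plan is miscalculated, and N = 90 stands. What it decides is whether the trial can answer its own superiority question. The conclusion rests on reading the exploratory sentence as it is worded and on the published text alone. If the authors meant only the secondary endpoints, the defect is one of wording, but the remedy is the same. It would go too far to say that the trial lacks a primary endpoint, that its result would be worthless as evidence, or that its false-positive risk is 34%.

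**What to change.** Choose one of two routes, and record it before any outcome data are compared by arm.

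1. **Confirmatory.** State in {20a} that the treatment coefficient for NRS change from baseline to 6 months, in the primary model, is the single confirmatory test at two-sided alpha 0.05. Limit the exploratory label to all other analyses, including every 12-month analysis. Make clear that the primary model refers to 6 months, and either assign the bracketed 12 to the secondary analysis or remove it. Since {20a} allows up to four further covariates without naming them, fix these at the same time; otherwise the confirmatory test is not fully defined.
2. **Exploratory.** Keep the sentence, and withdraw the superiority hypothesis in {7} and the high-evidence claims in the Abstract, Objectives and Discussion.

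The first route fits the rest of the protocol better. Trial status reports recruitment as ongoing, so this is a short protocol amendment rather than an editorial correction. It changes no procedure, visit, data collection or enrolment target.
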